### Objectives

The current pilot study aims to evaluate the feasibility, acceptability, and potential effectiveness of FAME to reduce parental mental health problems and improve family functioning. As families living in family locations might suffer from increased levels of distress, we expect these families to have more difficulties concerning the parent-child relationship, parental symptoms, and family functioning than families living in asylum centres. Therefore, baseline distress levels of both categories of families will be compared. Specifically, the objectives are to determine:Whether it is feasible to offer FAME to families living in Dutch asylum centres and family facilities.Whether FAME is acceptable to asylum-seeker families.Whether undergoing FAME coincides with a reduction in parental symptoms of anxiety and depression and improvement in family functioning.Baseline differences and similarities in the parent-child relationship, parental symptoms of anxiety and depression, and family functioning between families living in asylum centres and families living in family facilities.

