## Methods/design

### Trial design

An uncontrolled, two-group pre-test-post-test design will be conducted, using a mixed-methods approach. Standardized questionnaires, semi-structured interviews, an observational scale, and a (self-constructed) programme integrity list will be used. The programme, including measurements, will take approximately 10 weeks per group.

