### Statistical analysis

#### Analysis of quantitative data

Quantitative data-analysis will be conducted using SPSS 23 (IBM Statistics). Descriptive statistics of demographic data, the programme integrity list, and the rating scales will be presented for all participants. For continuous variables, means, standard deviations, medians, and ranges will be reported. For categorical variables, numbers and percentages will be reported.

To test the hypothesis that families living at family facilities have more problems concerning the parent-child relationship and family functioning and higher parental symptoms of anxiety and depression than families living at asylum centres, pre-test scores on the EAS, PHQ-4, and SCORE-15 will be compared between these two groups using independent *t* tests.

To evaluate whether undergoing FAME coincides with a reduction in parental symptoms of anxiety and depression and improvement in family functioning, differences between the pre- and post-test scores on the SCORE-15 and PHQ-4 will be calculated. If more than 40 participants have completed the pre- and post-test measures, a mixed-design ANOVA will be executed. However, if there is a large amount of missing data, or if less than 40 participants have completed pre-test and post-test measures, two independent *t* tests will be executed. In addition to statistical significance, it is important to report any meaningful clinical change when studying the impact of an intervention. Calculating the Reliable Change Index (RCI), as proposed by Jacobson and Truax [31], allows us to do so. Using the RCI, we will calculate whether the differences in the scores between *t*_1_ and *t*_3_ are greater than the measurement error. A calculated RCI larger than |1.96| indicates a clinically reliable change with 95% certainty. The RCIs allows us to determine the numbers of participants improved, unchanged, and worsened from *t*_1_ to *t*_3_.

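### The small-sample fallback for pre-post change names two independent t tests, which as two-sample tests do not validly test change within the same parents

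*Protocol article*

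**What the plan says.** The third objective in the Protocol article (Objectives) is to determine "Whether undergoing FAME coincides with a reduction in parental symptoms of anxiety and depression and improvement in family functioning". Table 3 has parents completing the SCORE-15 and PHQ-4 at t1 and again at t3.

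Under Analysis of quantitative data, this objective is served by a paragraph stating that "differences between the pre- and post-test scores on the SCORE-15 and PHQ-4 will be calculated". The test then depends on how many people complete:

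- Main rule: "If more than 40 participants have completed the pre- and post-test measures, a mixed-design ANOVA will be executed".
- Fallback: "if less than 40 participants have completed pre-test and post-test measures, two independent *t* tests will be executed". The same fallback has a second trigger: "if there is a large amount of missing data".

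The preceding paragraph uses the same term for the baseline comparison of family facilities with asylum centres, whose scores "will be compared between these two groups using independent *t* tests". There it has its standard meaning, a test between two unrelated groups. The pre-post paragraph also plans Reliable Change Indices to "determine the numbers of participants improved, unchanged, and worsened from *t*_1_ to *t*_3", so each person's two scores will be linked.

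**The concern.** The objective is a within-person contrast. The main rule can deliver it: in a mixed-design ANOVA with two time points, the time effect is a within-person comparison. The fallback names a test for unrelated samples, in the same section where that term plainly means such a test. The sentence does not say which two samples are compared, and both possibilities miss the objective. One discards the link between a parent's two scores. The other compares location types.

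At stake is the statistical answer to one of four objectives, in the branch used when numbers are small or data are missing. The Discussion warns that relocation and deportation may raise dropout. It also hopes that the study will supply parameters for the sample size of later studies, and a standard error that ignores pairing would be a poor input for that.

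**Working it through.** **Inputs from the article.** Same parents at t1 and t3 (Table 3); fallback below 40 completers, so at most n = 39; two outcomes; two location types. The article gives no power, effect size, SD or t1-t3 correlation for this test, so it has no figure of its own to reproduce.

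**Assumptions.** Equal SD of 1 at both times, normal scores, two-sided alpha 0.05, correlation r = 0.3, 0.5 or 0.7, true change d = 0.4 SD (and 0.8 SD for contrast).

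**Reading A: t1 against t3 as two samples.**

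- SE of the independent test = sqrt(2/n) = sqrt(2/39) = 0.226.
- SE of the paired test = sqrt(2(1-r)/n) = 0.189, 0.160 and 0.124 for the three values of r.
- Ratio = 1/sqrt(1-r) = 1.20, 1.41 and 1.83.

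Paired power comes from the noncentral t distribution with 38 degrees of freedom and noncentrality d/SE; for d = 0.4 this is 2.11, 2.50 and 3.22. The independent test was simulated on the same correlated data.

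| r | SE ratio | Type I error, independent (nominal 5%) | Power at 0.4 SD, independent | Power at 0.4 SD, paired | Power at 0.8 SD, independent | Power at 0.8 SD, paired |
|---|---|---|---|---|---|---|
| 0.3 | 1.20 | 2.0% | 40% | 54% | 97% | 98% |
| 0.5 | 1.41 | 0.6% | 38% | 68% | 98% | 99.8% |
| 0.7 | 1.83 | below 0.1% | 36% | 88% | 99.6% | over 99.9% |

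The share of paired power lost at 0.4 SD is 1 - 40/54 = 26%, 1 - 38/68 = 44% and 1 - 36/88 = 59%. At 0.8 SD it is 2% or less.

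**Reading B: change scores compared between location types, one test per outcome.** The pairing is kept, so the table does not apply. The null hypothesis, however, is equal mean change in the two location types. If every parent improves by 0.4 SD in both, that hypothesis is true and the test is significant about 5% of the time, the chance rate. If location is the between factor of the ANOVA (the article does not name it), this test matches the time-by-location interaction, not the time effect that objective 3 needs.

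**Missing-data trigger.** An unpaired test could take every t1 score and only the t3 scores of those who remain. With no change in anyone, the shift in means equals the dropout share times the t1 gap between leavers and stayers. Assuming 40% dropout and leavers 0.5 SD worse at t1, this is 0.4 × 0.5 = 0.20 SD of apparent improvement. The article does not say that scores would be used in this way.

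**The case against.** The strongest reply is that the sentence is ambiguous. The paragraph has just spoken of pre-post differences on two outcomes, and Trial design says that "An uncontrolled, two-group pre-test-post-test design will be conducted". The authors may have meant one test of change scores per outcome, or may have used the word loosely for two separate tests. This stands to the extent that reading A cannot be stated as fact. It does not rescue the sentence: reading B tests another question, and the loose reading still requires the paired form to be written down.

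Four further points limit the size of the problem, and they stand.

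- With positive correlation, reading A errs on the cautious side and leaves the mean change among completers unaffected.
- The Reliable Change Index counts give a within-person description whichever test is used.
- The article plans about 90 parents. If they are the participants counted, fewer than 40 completers means losing at least 51 of 90, or 57%; a 40% dropout would leave 54. The article gives no dropout figure, so the numerical trigger may never be reached. The missing-data trigger has no threshold.
- This is an uncontrolled pilot that disclaims attributing effects to the programme. That lowers the consequence, but the article still plans to report statistical significance for this objective.

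A reader might infer that most of the power is lost, or that a real reduction would usually be missed. The article does not support either. Without a stated correlation or effect size, the loss runs from almost nothing for large changes to more than half for small changes with moderate to high correlation. At a change of 0.5 SD and n = 39, the independent test still has about 60% to 64% power for r from 0.3 to 0.7.

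A reader might also infer that attrition will create a false effect. That needs both an all-available-scores comparison, which the article does not state, and assumed selective dropout.

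**Conclusion.** The fallback is wrong as written. As a two-sample test it either ignores the pairing or tests a difference between location types, and in neither form does it validly test whether the same parents' scores changed. This conclusion needs no numerical assumption.

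The size does. If t1 is compared with t3, the standard error is 1.20 to 1.83 times too large for r between 0.3 and 0.7, the test is conservative, and at n = 39 power for a 0.4 SD change falls by 14 to 52 percentage points (54 - 40 and 88 - 36). Near 0.8 SD the loss is negligible. Possible loss of more than half the power is a fair statement; loss of most of it as a general result is not. Bias from selective dropout is a risk under one possible use of the missing-data trigger, not something that the article specifies.

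**What to change.** Replace the two independent t tests by a paired t test of the t1-t3 change for each outcome (SCORE-15 total and PHQ-4 total), report the mean change with its 95% CI, and state that the contrast is within person. If a comparison of change between location types is also wanted, list it as a separate question. A linear mixed model that uses incomplete pairs is an optional alternative when data are missing; it is not needed to correct the error.

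The cost is one sentence in the analysis section. The scores are already linked by person for the Reliable Change Index, so no new data are needed.

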### Participants

Study participants will be recruited from the asylum-seeker family population in the Netherlands. Families will be selected through convenience sampling. Eligible families must meet the following criteria: (1) at least one caregiver participates in FAME, (2) at least one child aged 0–18 participates, and (3) the family lives in an asylum centre or family facility. Participants who are not able to function in a group, as reported by health teams of the family facility or asylum centre, are not eligible for this study. For example, participants who are likely to experience difficulties communicating in a group setting as a result of severe psychiatric illness, such as psychosis, will be excluded. Families with psychiatric problems, such as posttraumatic stress disorder or depression, who are likely to be able to benefit from FAME are included in the study. This will be discussed with the health teams prior to inviting the families to take part in the information session about FAME. Each group will include approximately five to eight families. Families will be divided over the groups based on the age of their child (0–5, 6–12, 13–18). However, this division cannot be followed strictly, for example, because some families have children in more than one age category. Therefore, the division will be used merely as a guideline. If there are multiple children in a family, parents are asked with which child they experience most difficulties and will be allocated to the age group of that child. All children of the family are invited to take part in the programme.

As this is a pilot implementation and evaluation of a programme that has not been studied previously, it was not considered appropriate to conduct a reliable sample size calculation. We aim to include approximately five living locations. In each location, we will recruit two groups of approximately six families. This will result in a total sample size of approximately 60 families (5 × 2 × 6). One or two parents and approximately one to two children of each family will take part, resulting in a total number of approximately 90 parents and 90 children.

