### Measurements

#### Quantitative

##### Parents

Family functioning will be measured using the Systemic Clinical Outcome and Routine Evaluation (SCORE-15; [20]). The SCORE-15 is a 19-item self-report questionnaire that can be used to monitor and report indicators of progress in systemic therapy. It offers an overall measure of family functioning as well as sub-scale scores on the dimensions: strength and adaptability, overwhelmed by difficulties, and disrupted communication. The validity of the SCORE-15 as an index of therapeutic change has been established. The questionnaire demonstrates good test-retest reliability, construct validity, and responsiveness in terms of clinical and reliable change [21, 22].

Parental symptoms of depression and anxiety will be assessed using the 4-item Patient Health Questionnaire for Depression and Anxiety (PHQ-4; [23]). The PHQ-4 has been validated in the general population. The total score is an index of anxiety and depression severity [24].

The following demographics of the participating family members will be collected: age, gender, country of origin, time spent in the Netherlands, number and age of family members, and educational level.

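### The plan offers the Reliable Change Index as its measure of meaningful clinical change, with 95% certainty, but by its own definition the index shows only change beyond measurement error

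*Protocol article*

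**What the plan says.** In the protocol article, the subsection on analysis of quantitative data sets out the RCI in five steps.

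- Purpose, beyond statistical significance: "it is important to report any meaningful clinical change when studying the impact of an intervention".
- Tool: "Calculating the Reliable Change Index (RCI), as proposed by Jacobson and Truax [31], allows us to do so".
- What the tool does: "we will calculate whether the differences in the scores between *t*_1_ and *t*_3_ are greater than the measurement error".
- Decision rule: "A calculated RCI larger than |1.96| indicates a clinically reliable change with 95% certainty".
- Output: "The RCIs allows us to determine the numbers of participants improved, unchanged, and worsened".

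The paragraph gives no other criterion for clinical change on either scale. Elsewhere, under Measurements (Parents), the article credits the SCORE-15 with "responsiveness in terms of clinical and reliable change", which names clinical change and reliable change as two separate properties.

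**The concern.** The third step is a correct description of the RCI, and it does not deliver what the first two promise. A difference larger than measurement error is detectable. Whether it matters to the parent, or moves the parent out of a symptomatic range, is a different question that the index does not address.

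The certainty wording is a second misreading. The 95% describes how often an unchanged parent stays within the limits. It is not the probability that a parent outside the limits has changed.

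At stake is how the three counts are interpreted. The RCI is brought in solely to report clinical change, so a reader following the plan would take the improved and worsened counts as clinical benefit and harm. Potential effectiveness is one of the stated objectives, and there is no control group to show what counts would arise without the programme.

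**Working it through.** **Inputs from the protocol article**
- Threshold of 1.96 in absolute value, paired with 95% (Analysis of quantitative data).
- Expected enrolment, one or two parents from each of about 60 families: "resulting in a total number of approximately 90 parents and 90 children" (Participants).
- 40 completers of both assessments, the number at which the plan switches its main pre-post analysis (Analysis of quantitative data).

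**Inputs assumed**
- Reliability r of each scale. The article gives neither r nor a baseline SD, so a range of 0.70 to 0.90 is used.
- Normally distributed measurement error.

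**1. The plan's own figure.** 2 × Φ(1.96) − 1 = 0.950. The pairing reproduces as a two-sided 5% error rate when there is no true change. The threshold is therefore right for reliable change.

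**2. What the threshold depends on.** RCI = (x₂ − x₁) / (SD × √(2(1 − r))). The smallest flagged change, in baseline SDs, is 1.96 × √(2(1 − r)):

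| Assumed r | Calculation | Threshold (SD) |
|---|---|---|
| 0.70 | 1.96 × √0.60 | 1.52 |
| 0.80 | 1.96 × √0.40 | 1.24 |
| 0.85 | 1.96 × √0.30 | 1.07 |
| 0.90 | 1.96 × √0.20 | 0.88 |

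The only things that move the threshold are the scale's reliability and SD. A drop of 1.0 SD counts as improved at r = 0.90 and as unchanged at r = 0.80, although its clinical meaning is the same.

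**3. What 95% does not mean.** Let q be the share of parents who truly improve, d their true improvement in baseline SDs, and suppose the rest do not change. A true improver is flagged as improved with probability p = 1 − Φ(1.96 − d/√(2(1 − r))), and an unchanged parent with probability 0.025. The share of improved flags that are true improvers is qp / (qp + (1 − q) × 0.025).

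- r = 0.70, q = 0.10, d = 0.5: p = 0.094, so 0.0094 / (0.0094 + 0.0225) = about 30%.
- r = 0.90, q = 0.50, d = 1.0: p = 0.609, so 0.3045 / (0.3045 + 0.0125) = about 96%.

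Across these assumed values the share runs from about 30% to 96%. It depends on quantities the index does not know, so no fixed certainty attaches to a flag. All of this concerns change of any kind, before clinical relevance is considered.

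**4. Flags from measurement error alone.** With no true change, 2.5% of parents with both assessments are flagged in each direction on each scale: 40 × 0.025 = 1.0, and 90 × 0.025 = 2.25. The figure for 90 requires every enrolled parent to complete both assessments.

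**The case against.** The strongest reply is that this is loose wording around a correct calculation. The decision rule says clinically reliable, not clinically meaningful. The sentence before it defines the index properly. The three categories carry no clinical label. The RCI is supplementary in a pilot, and the Discussion already says that effects cannot be attributed to the programme without a control group. Much of this stands: no threshold, test or count changes, and misreporting in a later paper is an inference. It does not remove the point, because the text does say that the RCI is how meaningful clinical change will be reported. The caveat in the Discussion concerns causation, not clinical meaning. A cut-off in a fuller document would leave the printed statement wrong.

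Three stronger readings are tempting and are not supported.

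- A reader might infer that many low-scoring parents in a preventive programme cannot count as improved because of the scale floor. The article gives no baseline distribution for either scale. It admits families with depression or posttraumatic stress disorder and expects raised distress in family facilities. How many parents sit near the floor is unknown.
- A reader might take 2.25 of 90 in each direction as the chance benchmark. The 90 is expected enrolment, and the Discussion expects dropout through relocation and deportation. The 2.5% also ignores regression to the mean, and it would not be symmetric if scale limits bind.
- A reader might conclude that published cut-offs must be applied. The article gives none, and it reports validation of the PHQ-4 in the general population only. Reporting reliable change alone, labelled as such, is defensible.

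**Conclusion.** The point holds as an error of interpretation. The value 1.96 is correct for reliable change. The statements that it captures meaningful clinical change, and does so with 95% certainty, are not, and the paragraph's own definition of the index contradicts the first of them.

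The numbers show scale only. The thresholds of 0.88 to 1.52 SD rest on assumed reliabilities. The 30% to 96% range also rests on assumed shares and sizes of true improvement. The 2.5% per direction assumes normal error and no true change; for short scales with whole-number scores it is approximate. The documents do not show that the improved count will be inflated or deflated in a particular direction, only that it cannot bear the clinical meaning the plan gives it.

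The correction should be made before analysis, but it does not threaten the design or the other analyses.

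**What to change.** Report the counts on each scale as *reliably improved*, *no reliable change* and *reliably worsened*, among parents with both the pre-test and the post-test, and state that denominator. Remove the statement that the RCI measures meaningful clinical change, the word for clinical in the decision rule, and the certainty wording. Say instead that 1.96 corresponds to a 5% two-sided error rate under no true change.

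Alongside the counts, give the 2.5% of completers per direction expected from measurement error alone, noting that it is approximate and does not cover regression to the mean or scale limits.

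If the sponsor wishes to keep a clinical-change claim, add a second criterion for each scale: reliable change together with crossing a clinical cut-off on the PHQ-4 or SCORE-15. Each cut-off should be fixed before analysis and justified for this population.

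The cost is a change of wording and a reference column in one table, plus a small extra analysis if the clinical claim is kept. The downside for the sponsor is a more modestly labelled improved count or, with the second criterion, possibly a smaller one.

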#### Analysis of qualitative data

All audio-recorded interviews will be transcribed verbatim. Data of the semi-structured interviews will be analysed using the qualitative data analysis software programme MAXQDA 10. The current study uses the General Inductive Approach as proposed by Thomas [32]. The approach is often used in qualitative data analysis. Data analysis is guided by the evaluation objectives. Using the General Inductive Approach for analysing qualitative evaluation data, the following five steps will be conducted: (1) initial reading of the text, (2) identifying specific text fragments related to the research questions, (3) labelling fragments to create categories, (4) reducing overlap and redundancy, and (5) describing the most important categories. These steps will result in three to eight outcome categories capturing the key aspects of the most important themes. Reliability of the qualitative data analysis will be assessed by independent parallel coding by two researchers during step 3 and 5.

